### Economic evaluation

A cost-effectiveness analysis will be performed to further investigate the impact of CBSP for patients and health and social care providers. Data on costs, service use and health status will be collected. Unit costs for each type of service will be derived from local and national databases and statistics. The main outcome of interest for a cost-effectiveness analysis is the likely cost-effectiveness of the CBSP intervention. Secondary analysis of the data will explore: the structural uncertainty associated with the trial design; the extent to which EQ-5D scores and QALY values are correlated with clinical outcome measures and discriminate between groups and sources of external data. Baseline covariates in patient clinical and socioeconomic characteristics and pre-study service use will be controlled for. Factors known to influence costs and QALYs (e.g. ethnicity, socioeconomic status) will be collected at baseline to statistically control for their impact. The data will also be used to inform sample size decisions for a definitive trial.

### Qualitative data

All interviews will be digitally audio-taped and transcribed verbatim. An inductive approach using Thematic Analysis [50] will be taken to elicit patterns within the data corpus using standard procedures involving identifying meaning codes and categories at both the semantic and latent level [50]. Data generation and analysis will continue in parallel, using the constant comparative technique. Disconfirming evidence will be sought, until thematic category saturation is achieved. Records of field notes will be maintained and reflections providing adjunctive data will be used to illuminate and justify interpretative decisions.

Analysis will be primarily conducted by the experienced qualitative applicants, but interim analysis will involve the wider multi-disciplinary research team, including the study’s service user reference group (SURG). Integrating data from different stakeholders, and researcher triangulation increases the trustworthiness of the final analysis [48].

## Discussion

The strength of the INSITE pilot RCT is that it will be one of the first to investigate the use of psychological therapies in acute psychiatric wards including a range of outcomes. It will explore key issues relating to experiences of suicidal patients and pragmatic issues that will inform a larger, definitive RCT that will examine the effectiveness of CBSP in inpatient settings, treatment uptake and recruitment. A limitation of the study design includes insufficient power to determine the effectiveness of key suicidality outcomes. The study sample was recruited from one mental health trust which is not representative of the wider inpatient environment.

Some of the issues that will need to be addressed include whether it is possible to recruit sufficient numbers of participants for a full-scale trial and to identify possible reasons why patients may, or may not, want to participate in the trial. We will discover if it is possible to retain participants in the intervention, both during their inpatient care and following discharge into the community. NHS services are often criticised for failings in the continuity of care, particularly for discharge from acute psychiatric wards when there is an increased risk of suicide [1, 15]. Therapy that begins on the ward and continues into the community may help to avoid such discontinuity. Working on the ward presents several challenges in itself and there are few precedents of psychological therapy being delivered in acute psychiatric settings. The study will investigate what features of ward activity need to be considered to successfully implement this intervention. CBSP has been employed in a community setting and for prisoners, but this study will examine how the therapy should be modified for acute inpatients.

It is also necessary to consider the most effective and sensitive outcome measures to detect meaningful change resulting from CBSP. Existing instruments measuring suicidal behaviours and ideas have limitations and may require refinement, particularly to reflect service-user defined outcomes of recovery from suicidality. The study would like to explore what training and support is required to maximise the contribution of service users to suicidality research. In order to determine whether CBSP is value for money, we will require data depicting the cost of current treatment to compare it to. Evidence of value for money is required to inform future NHS policy and funding decisions regarding CBSP. This information will have to be comprehensive to affect resource allocation. In addition to the research aims outlined, we are interested in the impact that the introduction of CBSP had on a number of patient and staff outcomes, including: patient experience of therapy; impact on suicidality; and ward staff views on the use of CBSP in the inpatient setting.

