**Methods/Design:**

A single blind RCT comparing treatment as usual (TAU) to TAU plus Cognitive Behavioural Suicide Prevention (CBSP) therapy (TAU + CBSP). Sixty participants (aged 18–65 years) who are suicidal, or have been within the past 3 months, will be recruited from NHS trusts in the North West of England. Our primary objective is to determine whether CBSP is feasible, acceptable and efficacious when compared to patients who receive TAU alone. Secondary aims are the impact of CBSP on suicidal thinking, behaviours, functioning, quality of life, service use and psychological factors associated with suicide. Assessments take place at baseline, 6 weeks and 6 months (end of treatment). The analysis will report on the feasibility and acceptability of CBSP. Qualitative data from staff and service users will inform feasibility and acceptability data.

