## Methods/Design

### Trial design

The Inpatient Suicide Intervention and Therapy Evaluation (INSITE) trial is designed as a single blind randomised controlled trial (RCT) with participants recruited from acute psychiatric wards from NHS trusts in the North West of England, UK. Sixty participants will be recruited and randomly allocated, using an independent source, to treatment as usual (TAU) or to TAU plus 20 sessions of Cognitive Behavioural Suicide Prevention Therapy (CBSP). TAU consists of medical and nursing care and medication as appropriate, plus multidisciplinary team management during inpatient stay. Following discharge, TAU would be variable depending on patients’ needs but typically would consist of multidisciplinary team management of community mental health team. Participants will be followed up at 6 weeks and 6 months (post intervention). The end of treatment is a fixed time and does not vary depending on treatment progress.

The project runs over three phases using a mixed-methods approach following the Medical Research Council’s (MRC’s) framework for developing complex interventions.

In phase 1, we conducted qualitative data collection from staff (*n* = 20) and patients (*n* = 20) investigating their views of inpatient care and on the implementation of CBSP, which has been used to inform the treatment and implementation protocol of the RCT. Phase 2 is the RCT evaluating CBSP reported here. Phase 3 will involve qualitative evaluation of staff and patient experiences and views of CBSP. A purposive sample of patients from both arms of the RCT will be sought to elicit a broad range of views regarding CBSP. This will include a balance of participants who have had a good outcome, those who have dropped out of the intervention and control participants. Interviews will explore participants’ and staff experiences and expectations of therapy, views on the content of CBSP and facilitators and barriers to implementation of the approach within inpatient settings. Informed consent will be obtained from all participants.

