### Recruitment and randomisation

Recruitment is over an 18-month period from May 2014 to the end of 2015. Eligible participants are identified by inpatient ward staff approached by trained research assistants or clinical studies officers from the Comprehensive Research Network (CRN). Participants deemed eligible to participate are provided with an information sheet detailing involvement in the trial and informed consent is taken 24 hours later should they wish to take part. Research assistants carry out a battery of assessments following which participants are randomly assigned to either TAU or TAU plus CBSP. Randomisation is statistician-led and pseudo-random, carried out using Sealed Envelope© Software [22] with group stratification by gender and history of self-harm. Allocation concealment is ensured as participant randomisation codes are not revealed until the participant is recruited into the trial. Participants are followed up by research assistants blinded to treatment allocation at 6 weeks and 6 months following baseline assessment. Procedures for maintaining blindness are developed for the trial, including steps and actions taken to ensure the blinding process is conducted correctly and to avoid jeopardising the blinding of the research assistant. During assessment participants are reminded by the research assistant to not disclose their treatment allocation. Blindness is monitored by the trial project coordinator who is not blinded to treatment and manages all follow-up appointments. Where blind breaches occur prior to follow-up appointments, subsequent data collection is allocated to an alternative research assistant to ensure all follow-up data is collected by blind assessors.

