### Data analysis

In accordance with the Consolidated Standards of Reporting Trials (CONSORT) principles [49], we will report all participant flow. Demographic data will be described using summary statistics (means and standard deviations or number and percentage).

The main efficacy analysis is on an intention-to-treat basis with data from all participants. Every effort will be made to follow up all participants in both arms for assessments and the analysis will use, where appropriate, statistical techniques for handling missing data. Descriptive statistics will be used to summarise the primary outcome measures.

The secondary outcome measures will be analysed using a linear regression model, allowing for the baseline measurement of outcome, treatment assignment and NHS trust as covariates, at each assessment point separately. The coefficient of the treatment assignment is an estimate of the between-group treatment effect, and can inform potential effect sizes for a future definitive trial. Point estimates and associated 95 % confidence intervals will be reported rather than tests of statistical significance (*p* values).

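### The article says both that recruitment is from several NHS trusts, with trust as a model covariate, and that the sample came from one trust; the setting and the trust term must be reconciled

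*Protocol article*

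**What the plan says.** Four places in the protocol article bear on this.

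- **Abstract, Methods/Design:** the sixty participants "will be recruited from NHS trusts in the North West of England".
- **Trial design:** the trial is described as an RCT with "participants recruited from acute psychiatric wards from NHS trusts in the North West of England, UK".
- **Data analysis:** the secondary outcomes go into a linear regression "allowing for the baseline measurement of outcome, treatment assignment and NHS trust as covariates, at each assessment point separately".
- **Discussion,** among the limitations: "The study sample was recruited from one mental health trust which is not representative of the wider inpatient environment".

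Three further places give context. Ethics and governance names a single host trust, but only as the body through which the trial is monitored. Recruitment and randomisation says allocation is done "with group stratification by gender and history of self-harm", so trust is not a stratification factor. Trial status says that recruitment is still open.

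**The concern.** The first two places describe a multi-trust setting and the third relies on it, since adjusting for trust has a purpose only if there are at least two. The Discussion says there is one. No sentence explains the difference, for instance by reporting that sites were added or withdrawn.

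Two things depend on the answer. The first is the setting. The trial exists to prepare a larger definitive trial, and its primary outcome is feasibility and acceptability. Whether uptake, attendance and retention were observed in one organisation or several decides how far those results carry, and a reader cannot tell. The second is the secondary-outcome model. Under one trust, its only adjustment beyond the baseline score is empty. The two factors that did shape the randomisation are not among the covariates listed.

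**Working it through.** The plan states no figure that could be reproduced here. The check sets the statements side by side and then asks what each reading does to the stated model.

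**Inputs**

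- Sample size: 60 (Trial design: "Sixty participants will be recruited and randomly allocated, using an independent source").
- Model terms: intercept, baseline score, treatment, NHS trust (Data analysis; the intercept is implied).
- Number of trusts: more than one, number not given (abstract and Trial design); one (Discussion).
- Stratification factors: gender and history of self-harm (Recruitment and randomisation).

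**Step 1: can the statements be reconciled?** The plural might be loose wording in the abstract and Trial design, but the covariate in the model makes that reading hard to sustain. The Discussion sentence might be a later report of what happened, but it is in the past tense while Trial status says recruitment continues, so it is not a final account of the sample. If the number of sites had been cut, the other three places would be out of date. On any reading, at least one current passage needs correcting.

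**Step 2: rank of the design matrix.** A factor with k levels, coded against a reference level, adds k − 1 independent columns. With one level, the trust column equals the intercept column and adds 1 − 1 = 0 to the rank. A numerical check with n = 60, 30 per arm and made-up baseline data gave:

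| Trusts | Columns | Rank | Trust term estimable? |
|---|---|---|---|
| 1 (trust entered as an indicator) | 4 | 3 | no |
| 2 | 4 | 4 | yes |
| 3 (reference-coded) | 5 | 5 | yes |

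**Step 3: effect on the treatment coefficient under one trust.** Adding a second constant column does not enlarge the space spanned by the other three. Fitted values and residual sum of squares are therefore unchanged. The residual variance is RSS / (n − rank) = RSS / (60 − 3) = RSS / 57 with or without the term, if all 60 are analysed. The treatment coefficient in the made-up data was 0.3815 in both fits. Estimate and interval are identical.

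**Step 4: the two readings compared**

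| If the truth is | Trust term | Abstract and Trial design | Discussion limitation |
|---|---|---|---|
| one trust | drops out, adjusts for nothing | overstate the setting | correct |
| several trusts | estimable, sensible | correct | wrong |

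**Step 5: cost of adding the strata.** Assume gender and history of self-harm are each coded at two levels. They then add two columns. With one trust the rank goes from 3 to 5 and the residual degrees of freedom from 57 to 60 − 5 = 55. With two trusts, rank 4 becomes 6 and the degrees of freedom go from 56 to 54. The loss is negligible.

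**The case against.** The strongest reply is that three places agree and the Discussion sentence is the outlier. If that sentence is the slip, the model has no fault and the matter is one line in a list of limitations. This stands as far as it goes: the constant covariate is conditional on the Discussion being right, and the article does not settle that. It does not remove the contradiction, because the sentence is current text and makes a direct statement about the sample.

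A second reply is that the consequence is small. That also stands. The regression serves secondary outcomes, in a trial that says it lacks power for effectiveness and will report intervals rather than p values. The primary outcome is summarised descriptively, with no trust term.

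A reader might go further and infer that under one trust the planned model fails, or that it would have to be altered in the light of the data. The documents do not support this. Only the trust coefficient is inestimable, and removing a one-level factor involves no choice that depends on results. A reader might also infer that the trial is in fact single-trust because one host trust is named. That naming concerns monitoring and says nothing about where participants are recruited.

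It may be said, finally, that adding the strata does not follow from the contradiction. That is right. It is a separate improvement to the same sentence of the plan, and it applies under either reading.

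**Conclusion.** The contradiction is real and unresolved in the article. Its main weight is on the description of the setting: either the abstract and Trial design claim a wider setting than the trial has, or the Discussion concedes a limitation it does not have. For the analysis, the effect is conditional and modest. With one trust the term is redundant (rank 3 of 4 columns), and the treatment estimates and confidence intervals are unchanged. With two or more trusts it is estimable and nothing in the model needs repair on this account. No primary-outcome result or sample-size figure depends on it.

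The conclusion rests on reading trust as a categorical covariate in a model with an intercept, which is the ordinary meaning of the Data analysis text. The benefit of adding the stratification factors depends on how strongly they predict each outcome. The article gives no figures for that, so no gain in precision is claimed here.

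**What to change.** State the number of recruiting trusts once, and use it consistently in the abstract, Trial design, Data analysis and Discussion.

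- **If one trust:** describe the trial as single-trust in the abstract and Trial design, delete NHS trust from the regression, and keep the limitation.
- **If several trusts:** give the number, keep trust in the model as a categorical term, and correct the limitation.
- **In either case:** add gender and history of self-harm to the covariates for the secondary outcomes, so that the analysis reflects the stratified randomisation.

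The cost is wording. Both stratification factors have to be recorded before allocation, so no data are added. As recruitment is reported as still open, the change can be made before the outcome analysis.

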## Trial status

We are currently recruiting participants for our trial.

## Abbreviations

BHS: Beck Hopelessness Scale
BSSI: Beck Scale for Suicidal Ideation
CBSP: Cognitive Behavioural Suicide Prevention
CBT: Cognitive Behavioural Therapy
CDS: Calgary Depression Scale
CSS: Coping in Stressful Situations
EQ-5D: EuroQol
GCP: Good Clinical Practice
GP: General Practitioner
CRN: Comprehensive Research Network
INSITE: Inpatient Suicide Intervention and Therapy Evaluation
NICE: National Institute for Health and Care Excellence
NIHR: National Institute for Health Research
PANSS: Positive and Negative Syndrome Scale
PSP: Personal and Social Performance Scale
PSYRATS: Psychotic Symptoms Rating Scales
QALY: Quality-Adjusted Life Year
RCT: Randomised Controlled Trial
SAMS: Schematic Appraisal Model of Suicide
SBQ-R: Suicidal Behaviours Questionnaire-revised
SCI: Sleep Condition Indicator
SCQ: Self-Concept Questionnaire
SPS: Suicide Probability Scale
TAU: Treatment As Usual
VOICE: Views on Inpatient Care
VOTE: Views on Therapeutic Environment
WAI: Working Alliance Inventory
WHOQOL-Brief: World Health Organisation Quality of Life-Brief
